### Secondary outcome

Assessment of secondary outcomes will begin from initial dressing application and continue until the 12-month follow-up review as illustrated in Fig. 1 and Table 2.

### Acute pain

An 11-point numeric rating scale-pain (NRS-P) scores pain from 0 (no pain) to 10 (worst possible pain) [56, 57]. A proxy report of pain (NRS-P Proxy) by guardians of all participants will be the primary approach for acute pain. The Face, Legs, Activity, Cry and Consolability (FLACC) scale is an observational pain measure that has been validated for peri-procedural pain in children [58, 59] and scores pain intensity by rating five behaviours on a 3-point scale (0 to 2): face, legs, activity, consolability and cry. The revised Faces Pain Scale-Revised (FPS-R) utilises a horizontal scale of six facial expressions with assigned numeric values from 0 to 10 (0, 2, 4, 6, 8, 10), with 10 denoting maximal pain intensity [60]. Acute peri-procedural pain will be assessed subjectively by self-report from participants aged ≥ 8 years who are competent at seriation testing using the NRS-P and FPS-R pain scales. Behavioural observations will be made by both clinicians (FLACC scale) and guardian of all participants (NRS-P Proxy).

All sedation and analgesia administered at the dressing change will be documented. Pain assessments will be completed before and after dressing removal and application. This will be adhered to as much as is practically possible. In some circumstances, such as whilst under general anaesthesia, it will not be able to document participant self-report nor behavioural observations. Peri-procedural distraction techniques including bubbles, food, mobile device and toy that are part of standard care will also be recorded.

### Itch

Acute post-burn pruritis will be measured with an 11-point itch NRS-I (0 = no pruritis to 10 = worst imaginable pruritis) until the wound is ≥ 95% re-epithelialised. Participants ≥ 8 years will self-report (NRS-I). A proxy report of participant itch (NRS-I proxy) will be taken from the accompanying guardian for all participants and will the primary approach for itch. The NRS-I has shown good correlation when compared with visual analogue scale and Itch Man Scale and is easier to use in the evaluation of itch intensity [61, 62]. The itch item of the Patient and Observer Scar Assessment Scale (POSAS) will be used to assess chronic pruritis and will be evaluated by all participants 8 years or older as well as by all guardians (POSAS Patient) and by an investigator (POSAS Observer) [63].

### Scar severity

The re-epithelialised wound will be evaluated for the severity of scars using objective (ultrasonography and colorimetry) and subjective (POSAS and Brisbane Burn Scar Impact Profile (BBSIP)) measures [63–66]. The objective measures are the principal approach based on evidence of the ability to detect change. Scar thickness will be measured using the portable Venue40 MSK® Ultrasound machine (GE Healthcare, Fairfield, CT, USA). Ultrasound test-retest and interrater reproducibility of scar thickness is acceptable for paediatric scars [67].

Scar colorimetry will be evaluated with the DSM II ColorMeter® (Cortex Technology, Hadsund, Denmark). This device uses tristimulus reflectance, colorimetry and narrow-band photometry to assess scar lightness (L*), erythema (a*) and pigmentation (b*) [68]. An average of three measurements of L*, a*, b* from both the scar and healthy skin will be recorded. The primary measure of scar pigmentation and scar erythema will be L* and a* respectively.

Both the investigator and guardian of all participants will complete the POSAS. This survey assesses scar thickness, vascularity, pliability, pigmentation and relief, as well as patient scale items of itch, pain, colour, stiffness, thickness and irregularity [63]. The BBSIP physical scar subscales and BBSIP sensory subscale will also measure scar severity [64–66]. An investigator having completed scar assessment training to the satisfaction of the occupational therapist at the study site will complete the scar assessments of all participants.

### Health-related quality of life (HRQOL)

The BBSIP measures HRQOL and patient-reported scar characteristics for individuals with burn scars [64–66]. The Child Health Utility 9D (CHU9D) is a preference-based measure that assesses both participant HQROL and resource utilisation of the interventions [69–72]. Participant guardians will complete both HRQOL assessments for all participants.

### Treatment satisfaction

Treatment satisfaction is a patient-reported outcome [73] that guides quality of service delivery by a treating health service provider. In a study of parents (*n* = 62) of children receiving burn treatment, the perceived support and respectful communication by clinicians was strongly associated with the quality of received care [74]. Both clinicians and participant guardian will complete an 11-point NRS (0 = not at all satisfied to 10 = extremely satisfied) to measure treatment satisfaction.

### Ease of dressing application

The ease of dressing application will be assessed using a questionnaire regarding the dressings (application ease, dressing conformability, dressing application duration) including additional space for comments by treating clinicians.

### Healthcare resource use

Healthcare resource use related to the management of burn injuries will be collected for each patient from the perspective of the healthcare provider with a 12-month time-horizon. Healthcare resource use to be collected for each participant will include trial interventions and other wound management-related resource use. In addition, product(s) used in wound and scar management as well as associated clinician labour time (e.g. for assessments and treatments during outpatient clinic appointments). Resource use for burn-related hospitalisations (e.g. intensive care admission) will also be collected. Resource use will be costed at market rates (e.g. industrial award rates for clinician labour time, standing offer arrangement rates for products supplied, values consistent with the (Australian) Independent Hospital Pricing Authority for hospitalisation costs).

## Data management

### Sample size estimate

The sample size estimate conducted for this trial is based on the primary outcome of TTRE. Using the Power Analysis and Sample Size (PASS) software (version 11.0.7; PASS, NCSS, LLC), a two-sided logrank test procedure was used. A total sample size of 84 subjects (28 participants per group) that accounted for a 10% attrition rate would achieve 80% power at a significance level of 0.05 [10, 75, 76]. A clinically important difference of 4 days for re-epithelialisation was used for the sample size estimation.

### Randomisation and allocation

To reduce the chance of prediction of treatment allocation, a procedure which randomly allocates participants in groups using a random step size will be used [77]. The randomisation sequence will then be uploaded into Research Electronic Data Capture (REDCap) randomisation module [78] by a third party person not associated with the study. Upon obtaining informed consent for the participation, baseline data (participant demographics including Fitzpatrick Skin Type, burn injury time, depth, TBSAB, injury mechanism and history of first aid prior to enrollment) will be collected. An investigator aligned with the study will complete the randomisation using REDCap and inform the treating clinicians of the allocated intervention group.

### Blinding

Once data collection is complete, a panel of burn wound specialists inclusive of preselected burn surgeons and nurses will conduct a blinded review of wound and scar imaging. Any possible identifying material that could indicate to the blinded assessors, which group the participant, was allocated to, will be removed from images. The participants and their care providers will be blinded to their intervention assignment. Although it will be unavoidable to detect remnants of silver dressing in some cases, it is anticipated that it will be almost impossible to differentiate between the group B and group C. An experienced radiographer from the study centre will complete blinded assessments of scar thickness.

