**Table 1 Tab1:**
[figure not shown]
Initial dressing application procedure

*RES*^*TM*^ Regenerative Epidermal Suspension, *ACH* Autologous cell farvesting, *FR* French gauge

Objective burn depth will be measured with the Moor LDLS-BI Laser Doppler Imager® (Moor Instruments Ltd., Axminster, and Devon, UK). The reported sensitivity and specificity of Laser Doppler Imaging (LDI) in predicting outcome of paediatric injuries when compared with clinician assessment ranges from 80.6–97% and 76.9–100% [45–47], respectively. The assessment of burn depth by the attending burns surgeon will be taken as the primary approach. Burn depth assessed with LDI will be the secondary approach and measured at the initial dressing application after randomisation. Burn depth assessment using LDI in the first 48 h post-burn injury has been showed to be accurate [48–51] and is used to record burn depth progression and not guide clinical practice at the study site.

A three-part process will be required for the initial dressing application of participants in group B that includes harvesting of donor skin, preparation and application of the ASCS to the wound followed by Biobrane® and secondary dressings. A suitable donor site, where possible, will be identified adjacent to the wound. The size of skin sample will be based on the TBSAB as determined by the RES™ preparation guidelines. A donor sample of healthy skin will be obtained at a depth of 0.15 mm (0.006 in.) in depth using a pneumatic dermatome (Zimmer, Dover, Ohio, USA). The correct thickness of donor is evidenced by an almost translucent sample that leaves behind pinpoint bleeding at the donor site, the edges of the sample do not curl and there is an absence of the white dermis surface. Any excess RES™ if present will be applied to the donor site then dressed with Cuticerin**®** (Smith and Nephew Medical Ltd., Hull, UK). The sequence of secondary dressings used in groups B and C will maintain moisture, allow for absorption of exudate and a degree of compression to minimise disturbance of the fragile epidermal surface. Application of these dressing changes is not required under general anaesthesia unless otherwise indicated. The attending burns surgeon or paediatric surgery registrar assigned to the care of the patient will apply the RES™ and Biobrane®. Both doctors and nurses will apply the standard silver dressings.

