## Study outcomes

### Primary outcome: TTRE

Wound re-epithelialisation time is defined as the number of days from date of burn injury to ≥ 95% wound re-epithelialisation or date of skin graft as determined by the attending burns surgeon. Subjective assessment by an experienced burn surgeon is validated and reliable and will be the primary approach for TTRE [52, 53]. Objective assessment with three-dimensional (3D) digital camera imaging will be the secondary approach. Wound re-epithelialisaton will be expressed as a percentage using wound area (cm^2^) and perimeter (cm) calculated on the first dressing change day and the day a clinical assessment of ≥ 95% wound re-epithelialisation is made by the attending burns surgeon. The first dressing change is usually within 3 to 5 days after the burn injury. This allows for the burn wound to declare full extent and represent the maximal possible wound area in the absence of infection.

Images taken with the 3D LifeVizII System® (Quantificare S.A., Cedex, France) will be analysed using Dermapix® v3.0 (Quantificare S.A., Cedex, France). This fast, non-invasive 3D clinical imaging approach is ideal for children. The 3D LifeVizII System®/Dermapix® has been validated in the assessment of partial thickness burn injuries (intraclass correlation coefficient (ICC) 0.96, 95% confidence intervals (CI) 0.93–0.97) [54, 55]. However, the Dermapix® software is time-consuming as it requires the images to be first uploaded, then stitched and lastly, analysed. Hence, using Dermapix® does not provide a real-time analysis of the wound.

A second 3D camera, the Intel® RealSense™ Depth Camera D415 (Intel, CA, USA) with corresponding GPC 3D WoundCare (GPC, Swansea, UK) software will be used as a second secondary objective measure of TTRE. The reliability of the WoundCare Lite (ICC 0.985, 95% CI 0.905–0.996) [41] and instantaneous availability of analysed data output is advantageous over the 3D LifeVizII System®/Dermapix®. Validation in the paediatric burn wound population is currently in progress, as this technology is relatively new.

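### The protocol says care providers are blinded, yet treating clinicians are told the allocation, and the attending surgeon, one of that group, judges the primary outcome

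*Protocol article*

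**What the plan says.** All references are to the protocol article.

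- **Blinding:** "The participants and their care providers will be blinded to their intervention assignment". The same section plans a blinded review of wound and scar images by a specialist panel after data collection, and blinded scar-thickness measurement by a radiographer. It concedes that traces of silver will sometimes be visible.
- **Randomisation and allocation:** the investigator who randomises is to "inform the treating clinicians of the allocated intervention group".
- **Operative procedures:** "The attending burns surgeon or paediatric surgery registrar assigned to the care of the patient will apply the RES™ and Biobrane". For group A, "Both doctors and nurses will apply the standard silver dressings". Group B alone has donor skin taken with a dermatome and a separately dressed donor site.
- **Primary outcome: TTRE:** the end of TTRE is "≥ 95% wound re-epithelialisation or date of skin graft as determined by the attending burns surgeon". The section adds: "Subjective assessment by an experienced burn surgeon is validated and reliable and will be the primary approach for TTRE". Imaging with 3D cameras is a secondary approach, with wound area and perimeter "calculated on the first dressing change day and the day a clinical assessment of" at least 95% healing is made by the surgeon.
- **Abstract, Methods:** dressings after the first are changed every 3 to 5 days.
- **Sample size estimate:** the clinically important difference is 4 days.

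**The concern.** The blinding statement and the procedures cannot both be true. A clinician who is told the group, harvests skin for one arm only, and sprays cells or lays a membrane is not blinded. The section on ease of dressing application also asks treating clinicians to rate the dressing, which they can only do knowing what it is.

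This matters because the endpoint is a judgement. Both events that end TTRE, the healing call and the skin graft, are determined by the attending surgeon, who belongs to the group told the allocation. Evidence that surgeon assessment is valid and reliable does not protect against expectation when the arm is known. A reader who takes the blinding statement at face value would believe that this source of detection bias had been removed.

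**Working it through.** The protocol gives no figure for this point to reproduce. The check is a comparison of sections, followed by a sizing under stated assumptions.

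**1. Who knows the arm?**

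| Role | Blinding section | Other sections | Result |
|---|---|---|---|
| Treating clinicians | blinded | told the group; apply the products | not blinded |
| Attending surgeon judging TTRE | blinded, as a care provider | is a treating clinician; may apply the product | not blinded |
| Participants and guardians | blinded | donor harvest in group B only; Background describes silver dressings as non-transparent and Biobrane as transparent | doubtful (inference) |
| Image panel | blinded | silver sometimes visible | blinded, with a limit for group A |
| Scar-thickness radiographer | blinded | nothing contrary | blinded |

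**2. What can the 3D measurement detect?** It is described at two times: the first dressing change and the day the surgeon calls healing.

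- Call too early: the second image shows less than 95%, so the error is visible. No rule says what then follows.
- Call too late: the second image shows at least 95%, as it should. Healing at a previous visit leaves no trace in these two measurements.

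Late calls matter for the comparison. Delaying the call in the silver arm favours the other arms just as much as advancing it in theirs.

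**3. Size.** A call one visit early or late moves that child's TTRE by 3 to 5 days. That is an individual shift and should not be set directly against a group difference. The arm-level quantity is

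shift in arm mean = proportion of the arm affected × visit interval.

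The proportion is not in the documents; 10 to 40% is assumed.

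| Proportion (assumed) | 3 days | 4 days | 5 days |
|---|---|---|---|
| 10% | 0.3 | 0.4 | 0.5 |
| 25% | 0.75 | 1.0 | 1.25 |
| 40% | 1.2 | 1.6 | 2.0 |

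At a 4-day interval, 0.4/4 = 10% and 1.6/4 = 40% of the target difference.

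**4. Effect on false-positive risk (illustration only).** Take two arms with no true difference, 25 analysable per arm (28 × 0.9 = 25.2), and a normal approximation for two means. With z = shift / (SD × √(2/25)), the chance of two-sided p < 0.05 is Φ(z − 1.96) + Φ(−z − 1.96). For a 1-day shift and SD 4, z = 1/(4 × 0.283) = 0.88 and the chance is about 14%. It is about 11% at SD 5, 9% at SD 6 and 7% at SD 8. The SDs are assumed, and the planned analysis is logrank and Cox, so these figures show only the order of magnitude.

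**The case against.** The strongest reply is that surgeon assessment is the validated clinical standard, that dressings of this kind can rarely be hidden from those who apply them, and that the article already plans objective imaging and a blinded panel. Much of this stands. Open assessment by the surgeon is defensible if it is declared, and replacing the primary measure after recruitment began in May 2018 would have real costs.

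Several stronger readings are tempting, but the documents do not support them:

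- *The trial presents itself as blinded.* The Abstract and Study design call it a randomised parallel-group trial, not a blinded one. The claim is confined to the Blinding section.
- *The 3D measure is no check at all.* It can reveal early calls. Table 2, which holds the assessment timetable, is not shown, so more imaging may be scheduled than the text describes.
- *The panel is excluded from the primary outcome.* Its role is unstated, not ruled out.
- *One person applies the product and judges healing.* A registrar may apply it. What is shown is that the judging role belongs to the informed group.
- *The panel's date should become primary.* A date based on images alone would drop the graft component, using the surgeon's date for ungradable images would mix blinded and unblinded dates, and the panel may recognise group A from silver traces.

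None of this reconciles the blinding statement with the disclosure of allocation to treating clinicians.

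**Conclusion.** The concern holds. The blinding statement is wrong for care providers and unsupported for participants and guardians, and the primary TTRE, both healing and graft date, rests on the judgement of a role that knows the arm. The safeguards described do not close the gap: the 3D measurement misses late calls, and the panel has no stated TTRE role.

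The possible bias is about 0.4 to 1.6 days in an arm mean against a 4-day target, if 10 to 40% of one arm were shifted by one visit of about 4 days. That proportion is an assumption; the documents do not show that such a shift occurs or in which direction. What is established is the contradiction and the exposure, not an actual bias.

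**What to change.** 1. **Correct the Blinding section.** State that care providers, including the surgeon who assesses TTRE, are not blinded, and that participants and guardians cannot be assumed to be. State that the image panel and the scar-thickness radiographer are blinded, and that the panel's blinding to group A is limited where silver is visible.
2. **Keep the surgeon's date as the primary TTRE and pre-specify a sensitivity analysis on the panel's date.** Define that date as the first available dressing-change image rated at least 95% re-epithelialised, with skin graft still ending TTRE as in the current definition. Report agreement with the surgeon and the number of ungradable images by arm. If the two analyses differ, interpret the primary result with caution. The graft date remains an unblinded decision in both analyses, and the report should say so.
3. **Where images exist at each dressing change, report the 3D percentage at those visits as supportive only.** The article says that validation of the instantaneous software in paediatric burns is still in progress.

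The cost is a wording change plus some extra reading and analysis time. Some images may prove ungradable. The primary endpoint does not change.

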### Statistical analysis

In the exploratory stage, data will be graphed, and summary statistics will be calculated for all outcomes. Data will be analysed using the ‘Intention to Treat’ principle. The primary outcome data will use the survival analysis model (both Kaplan-Meier analysis and Cox proportional hazards regression), with the time to healing as the main outcome and dressing group as the explanatory variable. All other data will be analysed using appropriate methods for longitudinal data such as mixed model’s regression analysis or generalised estimating equations (GEE). A GEE is better suited for estimating population average effects whereas mixed models are better suited for understanding the source of correlation and its structure. Thus, they are complementary ways of analysing the data rather than opposing. It should also be noted that for symmetrical outcome variable distributions (such as normally distributed) both methods should give similar results. Statistical significance will be set at *p* < 0.05. The data set will be analysed with SPSS (IBM Corporation, Armonk, NY, USA) and Stata (StataCorp, College Station, TX, USA) software where appropriate.

### Data collection and storage

Data collection will be in the form of completion of questionnaires and clinical imaging (2D and 3D photographs, laser Doppler imaging and sonography), colorimetry, assessments of pain, itch intensity, treatment satisfaction, ease of dressing application, HRQOL, wound intervention fidelity, healthcare resource utilisation and scar severity as well as participant demographics, socioeconomic status and clinical characteristics. Data collection and management will be completed by an investigator and entered into the REDCap software [78] system for managing the data. At the study site, the de-identified data will be kept in a locked filing cabinet and backed up onto the Queensland University of Technology (QUT), Research Data Storage Service. This data will be stored for 15 years after the completion of the trial in accordance with National Health and Medical Research Council guidelines. Results of this study are to be published in peer-reviewed journals and presented at national and international burns conferences. This protocol was completed in accordance with the SPIRIT 2013 guidelines [79, 80].

## Discussion

The overall reported rate of hypertrophic scar formation in children ranges from 17 to > 50% in children [17]. To avoid the costly burden of managing burn scars and the impact on participants and families, current wound management approaches focus on shortening re-epithelialisation time. An ideal skin substitute provides effective and scar free healing. However, current wound management approaches incorporate some but not all properties of a functioning integumentary system thus the debate continues regarding how best to treat these burn wounds. For children with larger TBSAB, faster TTRE assists these burn survivors to begin the process of rehabilitation earlier, enables earlier return to routine daily activities and reduces scarring.

Effective pain management is of paramount importance, from both a psychological and clinical perspective in paediatric burn patients. Sub-optimal peri-procedural analgesia was significantly associated with a 2.2% delay in re-epithelialisation, for every point increase in pain measured using the FPS-R [81]. In addition, reducing the number of dressing changes may reduce the potential pain and distress associated with dressing changes. Post-burn pruritis causes much distress in children and has a moderate association with mental health [82]. Uncontrolled scratching hinders the re-epithelialisation process and potentially disrupts the fragile newly regenerated epithelium. In addition, the potential introduction of infective pathogens would also delay TTRE. Inevitably, a proportion of children post mixed partial thickness burn will develop a scar. A multi-disciplinary approach that incorporates both operative (contracture release, medical needling) and non-operative treatments (topical silicone, pressure garments) is vital to successful scar management. Efficient health resource utilisation improves the quality of health care provided to current and future children with mixed partial thickness burn injuries and most importantly enables clinicians to make informed decisions on best practice.

Based on past trials and studies at the study site, a limitation of this study is the anticipated large dropout rate. Potential attrition bias will be addressed by examining whether the extent and reasons for dropout are balanced across the groups [83]. Although different dropout rates across the three groups are not anticipated, a sensitivity analysis will be run to check for any differences. It is expected that random drop out will result in larger confidence intervals but not bias. In addition, if there is no imbalance, then attrition bias is not likely to be a problem [83]. Limitations associated with burn depth assessment and wound infection diagnosis will be adjusted for during statistical analysis. The BRACS randomised trial will add new knowledge regarding the comparative effectiveness of autologous skin cell suspension for the management of partial thickness and paediatric burn injuries.

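### Balance in dropout is taken to make attrition bias unlikely, and GEE and mixed models are said to agree without a missing-data condition; neither is safe for the 3, 6 and 12-month secondary outcomes

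*Protocol article*

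**What the plan says.** Two parts of the protocol article bear on this.

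- **Discussion (limitations).** Drawing on past work at the site, it states that "a limitation of this study is the anticipated large dropout rate". Attrition bias is to be handled by seeing whether the amount of dropout and the reasons for it are balanced across the three groups, with a sensitivity analysis to look for differences between groups. Random dropout is expected to widen intervals without causing bias. Citing a source, it concludes that "if there is no imbalance, then attrition bias is not likely to be a problem".
- **Statistical analysis.** All non-primary outcomes are to be analysed by longitudinal methods such as mixed models or GEE. The section gives the two methods different purposes and continues: "Thus, they are complementary ways of analysing the data rather than opposing". It adds that they should give similar results when the outcome distribution is symmetrical. It attaches no condition about missing data and does not choose between them.

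The only attrition figure is under Sample size estimate: "A total sample size of 84 subjects (28 participants per group) that accounted for a 10% attrition rate". That calculation is for the primary outcome.

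**The concern.** Balance describes how many children leave and what was recorded as the reason. It does not show that the children who left resembled each other in outcome from arm to arm. The same number lost to follow-up can be logged in each arm while different kinds of children are missing. The planned sensitivity analysis looks at dropout itself, so it repeats the balance check and does not test what happens if dropout is not random.

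The open choice of method adds to this because the two methods rest on different assumptions:

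- Unweighted GEE generally needs data missing completely at random (MCAR). It is nearly unbiased when dropout depends on recorded outcomes only if the working correlation is suitable.
- A likelihood mixed model needs only missing at random (MAR): dropout may depend on outcomes already recorded.
- Neither covers dropout that depends on the unseen value (MNAR).

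Symmetry of the outcome does not remove this difference. Scar severity, quality of life and chronic itch at 3, 6 and 12 months depend on families returning, and a family whose child has little scarring may see less reason to come. That last step is clinical reasoning; the protocol does not state it. At stake is a check that passes while a between-group contrast is biased, and a choice between two methods that could disagree.

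**Working it through.** **1. The plan's own attrition figure.** Taking 25 evaluable children per group (inferred, not stated), 25 / (1 − 0.10) = 27.8, rounded up to 28, and 3 × 28 = 84. The arithmetic is consistent, but it concerns numbers and says nothing about bias. The expected dropout is called large without a figure, a time point or a named outcome.

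**2. Inputs of the illustration (all assumed except the group size).** Two arms; three visits; outcome SD 1; correlation 0.6 between any two visits; true difference 0 at the last visit. The same fraction *d* drops out of each arm and misses the last two visits. The children who leave are those highest on an index: the driving score plus independent noise of SD 1. In the arm-opposite case the sign of the score is reversed in the second arm. The group size of 28 is the protocol's.

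**3. Closed form for the observed-case difference** (the same as GEE with independence working correlation). The index correlates 1/√2 with the driving score. Removing the top fraction *d* shifts the mean of the retained index by −φ(z)/(1 − d) in SD units, where z is the (1 − d) normal quantile. With opposite signs the two shifts add:

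bias = 2 × r × (1/√2) × φ(z)/(1 − d)

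Here r = 0.6 if the first score drives dropout (MAR) and r = 1 if the last, unseen score does (MNAR).

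For d = 0.30: z = 0.5244, φ(z) = 0.3477, and φ(z)/(1 − d) = 0.4967.

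- MAR: 2 × 0.6 × 0.7071 × 0.4967 = 0.42 SD.
- MNAR: 2 × 1 × 0.7071 × 0.4967 = 0.70 SD.

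**4. Large-sample simulation, dropout equal in both arms, true effect 0.**

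| Mechanism | d | Observed-case / independence GEE | Likelihood analysis |
|---|---|---|---|
| MCAR | 30% | about 0 | about 0 |
| MAR, same in both arms | 30% | about 0 | about 0 |
| MNAR, same in both arms | 30% | about 0 | about 0 |
| MAR, arm-opposite | 10% | 0.17 | 0.00 |
| MAR, arm-opposite | 30% | 0.42 | 0.00 |
| MAR, arm-opposite | 40% | 0.55 | 0.00 |
| MNAR, arm-opposite | 30% | 0.71 | 0.50 |

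Dropout rates are identical in every row, so a comparison of rates cannot tell the rows apart.

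**5. Fitted models at 28 per arm** (MAR, arm-opposite, 30%; normal outcomes; 600 runs):

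| Method | Mean bias (SD) | False-positive rate |
|---|---|---|
| GEE, independence | 0.39 | 28% |
| GEE, exchangeable | 0.04 | 5.3% |
| Random-intercept mixed model | 0.00 | 4.5% |

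The Monte Carlo standard error is about 0.012 SD for each bias. The outcomes are symmetrical, yet independence GEE and the mixed model disagree. Exchangeable GEE does well here partly because the simulated correlation really is exchangeable.

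**6. One shared mechanism with a true difference of −0.5 SD** (a common dropout threshold, 30% overall). Dropout becomes 36% and 24%. The observed-case estimate is −0.43 and the likelihood estimate −0.50 under MAR; under MNAR they are −0.38 and −0.41. With 28 per group, those rates are 0.36 × 28 ≈ 10 children against 0.24 × 28 ≈ 7, a gap that could easily be read as balance.

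**The case against.** The strongest reply has four parts.

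- **The text is milder than a quick reading suggests.** A reader might infer that balance is treated as proof of no bias. The protocol says only that bias is unlikely, and it looks at reasons as well as extent. Nor does it call the two methods interchangeable: it separates their purposes and limits the claim of agreement to symmetrical outcomes. The sentence about random dropout is correct as written, and the cited source for the balance inference may attach conditions that cannot be seen here. All of this stands. What remains is that balanced extent and reasons still cannot exclude outcome-related dropout, and that the agreement claim omits the condition that matters.
- **The large figures come from a chosen adverse case.** If well-healed children stay away in every arm alike and there is no true effect, the bias is about 0. Arm-opposite dropout has no support in the documents, and recorded reasons might reveal it. This stands, so the figures illustrate a possibility and predict nothing about this trial.
- **Independence GEE is the least favourable version.** The protocol does not specify it, and exchangeable GEE nearly matched the mixed model. This also stands. It shows that the answer depends on a working correlation the protocol leaves open.
- **Model detail belongs in a statistical analysis plan.** True of covariates, weights and imputation as such, and leaving them out is not the point. The point is two statements the article does make: the inference from balance, and the unconditional claim of similar results.

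**Conclusion.** The concern holds in limited form. The inference from balanced dropout to unlikely attrition bias is not sound, and the named sensitivity analysis does not examine departures from random dropout. The statement that GEE and mixed models should agree for symmetrical outcomes needs a missing-data condition, all the more because the protocol itself expects large dropout.

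The size of any bias cannot be derived from the documents. Under the assumed inputs it runs from about 0 (MCAR, or one shared mechanism with no effect) to about 0.4 SD for independence GEE with arm-opposite MAR dropout of 30%. In that last case exchangeable GEE is off by about 0.04 SD and the mixed model by about 0. Under arm-opposite MNAR dropout the likelihood analysis is biased too (0.50 SD against 0.71 SD), so changing the model alone is not a full answer.

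A reader might go further and conclude that the follow-up results will be biased, or that the primary result is in doubt. The documents support neither. They give no dropout figure or mechanism for the 3 to 12-month visits, and time to re-epithelialisation is analysed by survival methods that the choice between GEE and mixed models does not touch. This should be corrected, but it concerns secondary outcomes only.

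**What to change.** For the secondary outcomes at 3, 6 and 12 months:

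1. Name a likelihood mixed model as the primary analysis, with group, visit and their interaction, all randomised children with any follow-up, and baseline burn depth and TBSAB (both already collected) as covariates.
2. Use GEE only with inverse-probability weights or after multiple imputation, and qualify the statement that the two methods give similar results.
3. Delete the inference that balance makes attrition bias unlikely. Keep the comparison of extent and reasons for dropout as a description.
4. Add a delta-adjusted sensitivity analysis: shift the values imputed for children who drop out by a range of amounts fixed in advance, including shifts that differ by group, and report whether the conclusions change.

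The cost is revised wording and a little extra programming. No new data are needed, and the sample size and primary analysis are unchanged.
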